# Prevention of radiotherapy induced enteropathy by probiotics (PREP): protocol for a double-blind randomized placebo-controlled trial

**DOI:** 10.1186/s12885-021-08757-w

**Published:** 2021-09-16

**Keywords:** Radiotherapy, Enteropathy, Probiotics, Efficacy, Safety

## Abstract

**Background:**

Radiation induced enteropathy is a common complication of radiotherapy for pelvic tumors and adversely affects patient quality of life. Probiotics are thought to restore bowel microflora to optimal levels and reinforce intestinal barrier capacity. Although probiotics are effective in the treatment of radiation induced enteropathy, less is known about their efficacy to prevent radiation induced enteropathy.

**Methods:**

This double-blind randomized placebo-controlled study will investigate the efficacy of probiotics to prevent radiation-induced enteropathy in patients with gynecologic or urologic cancer who received pelvic radiotherapy. The study is designed to enroll 248 eligible patients, who will be randomized 1:1 to a probiotic or placebo group. Toxicities will be evaluated using Common Terminology Criteria for Adverse Events (CTCAE) v5.0.

**Discussion:**

The primary aim of this study is to provide high level evidence for the ability of probiotics to prevent acute radiation induced enteropathy. The secondary aims are to determine the effects of probiotics on the incidence of chronic radiation induced enteropathy and the safety of probiotics in patients with gynecologic or urologic cancer.

**Trial registration:**

ClinicalTrials.gov (NCT03978949, Registered on 7 June 2019).

**Supplementary Information:**

The online version contains supplementary material available at 10.1186/s12885-021-08757-w.

## Background

Acute radiation induced enteropathy (RIE), which occurs within 3 months of treatment, has been reported in 60–80% of patients who receive pelvic radiotherapy [1]. Typical symptoms of RIE include diarrhea, nausea, vomiting, and belly cramps. These symptoms may cause dehydration, electrolyte imbalance, and malnutrition, which can adversely affect patient condition at the time of treatment. Treatment interruption or changes in the initial treatment plan may be required, which could compromise the likelihood of tumor control. Delayed RIE can also occur in long-term survivors of pelvic radiotherapy and may affect their quality of life [2].

The World Health Organization (WHO) has defined probiotics as “live micro-organisms which, when consumed in adequate amounts, confer a health benefit on the host” [3]. Probiotics have various effects on their hosts, including the production of antimicrobial bacteriocin and short chain fatty acids, lowering of gut pH, nutrient competition, stimulation of mucosal barrier function, and immunomodulation, although their exact mechanisms of action remain unclear [4]. Probiotics may help prevent and manage RIE by reducing the apoptosis of intestinal epithelial cells, promoting recovery from radiation damage, and enhancing local or systemic immune response against pathogens [5–9]. Two meta-analyses also reported that probiotics may be beneficial for RIE [10, 11]. However, these studies had several limitations. Most were small in size, containing relatively small numbers of patients. Although the largest study included 482 patients from Italy [6], there was no information about chemotherapy, with patients starting probiotics on the first day of radiotherapy, preventing the accumulation of live bacteria prior to treatment.

There are increasing interests in the relation between radiotherapy and the gut microbiome with recent publications of review articles [12, 13]. Both review articles expected that the probiotics could minimize the adverse effect, but pointed out that further robust randomized controlled trials are required. Herein, we plan the present Prevention of Radiotherapy induced Enteropathy by Probiotics (PREP) trial to establish high level evidence.

## Methods/design

### Study aim and design

The PREP study is a prospective, double-blinded, placebo-controlled, randomized trial ongoing at Asan Medical Center, Seoul, Korea. The primary aim of the study is to investigate the efficacy of probiotics, starting 2 weeks before radiotherapy, to prevent acute RIE in patients being treated with pelvic radiotherapy for gynecologic or urologic malignancies. Secondary aims include evaluations of the effects of probiotics on the incidence of chronic RIE and the safety of probiotics in patients with gynecologic or urologic cancer.

The design of the PREP trial is illustrated in Fig. 1. Patients diagnosed with gynecologic or urologic malignancies and scheduled to undergo pelvic radiotherapy will be screened and provided with an appropriate explanation about the PREP trial. Written informed consent will be obtained by radiation oncologists from patients who elect to participate in the study. After stratification by sex, participants will be randomly assigned 1:1 to the probiotics or placebo group using blocked randomization. Sex will be the single stratification factor, as patients with gynecologic malignancies have a greater tendency to require concurrent chemoradiotherapy, which affects the incidence of RIE. The block size and sequence for randomization will vary. The randomization sequence will be generated by a central web-based computer so that allocation will be concealed from the primary investigator who enrolls the patients. Neither participants nor physicians will be aware of their group assignments.

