### Inclusion criteria

Patients will be included if they [1] have histologically proven malignancies of the uterus, ovary, vagina, vulva, bladder, urethra, or prostate [2]; are aged > 20 years [3]; have an Eastern Cooperative Oncology Group performance score of 0–2 [4]; have an adequate hematologic condition within 6 months after enrollment, defined as absolute neutrophil count ≥1500 cells/mm^3^, platelet count ≥50,000 cells/mm^3^, and hemoglobin ≥8.0 g/dl [5]; have appropriate kidney function within 6 months after enrollment, defined as creatinine < 2.0 ng/dL; and [6] have appropriate liver function within 6 month after enrollment, defined as total bilirubin < 1.5 times the maximum normal value and alanine aminotransferase and aspartate aminotransferase < 2.5 times the maximum normal value.

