### Data collection and follow-up period

The primary endpoint will be the incidence of acute RIE, and the secondary endpoints will be chronic RIE and toxicities due to probiotics. Patient enrollment and treatment is expected to be completed within 2 years. Patient data on endpoints will be collected before the start of radiotherapy, every week during radiotherapy, every 3 months for the first 2 years after radiotherapy, and every 6 months subsequently for up to 5 years after radiotherapy (Fig. 2). All toxicities will be graded using CTCAE v5.0. The trial design and protocol adhere to the Recommendations for Interventional Trials (SPIRIT) criteria. The SPIRIT checklist and figure can be found in Supplemental Table S1.

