### Sample size and statistical analysis

Two proportion test in Power Analysis and Sample Size Software 2018 (NCSS, LLC. Kaysville, Utah, USA) was utilized to estimate the sample size. Based on the assumption that 30% of the patients in the placebo group and 15% of the patients in the probiotics group will experience grade ≥ 2 acute toxicities, 118 patients per group will be required to show a significant effect based on an alpha value of 0.05 and a beta of 0.2. Assuming a 5% dropout rate, 124 patients per group will be required (total, 248 patients).

Acute toxicities will be analyzed in the intention to treat population, with categorical variables in the two groups compared by the Chi-Square or Fisher’s exact test. To find the other confounding factors for RIE, univariate and multivariate logistic regression for acute toxicity will be performed. The times from the start of radiotherapy to acute grade ≥ 2 toxicities and to any chronic toxicities will be calculated using the Kaplan-Meier method and compared in the two groups using the log-rank test to compare survival curves between two groups. In the whole population, multivariate analysis, Cox proportional hazard model will be utilized to find the significant factor for the incidence of RIE in addition to the use of probiotics. Factors with *p* ≤ 0.2 in log-rank test will be entered in multivariate analysis. Descriptive statistics of all analyzed parameters will be provided, whenever appropriate.

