The largest prospective double-blind, placebo-controlled trial performed to date on the relationship between probiotics and RIE [6] found that the incidence of radiation induced diarrhea was significantly lower in the probiotics than in the placebo group (31.6% vs. 51.8%, *P* < 0.001), as was the incidence of grade 3 or 4 diarrhea (1.4% vs. 55.4%, *P* < 0.001). That study, however, did not provide information on chemotherapy, one of the major factors contributing to RIE, nor did it evaluate the incidence of chronic RIE. Furthermore, IMRT is frequently utilized in real-world clinical conditions for pelvic radiotherapy, suggesting the need to evaluate the effects of probiotics in patients undergoing IMRT.

Probiotics are generally considered safe in a healthy population [20]. However, it is essential to investigate the safety of probiotics in immunocompromised cancer patients. Case studies have reported that the probiotics Lactobacillus and Bacillus may cause infection in these patients, resulting in sepsis [26, 27]. However, a systematic review of the use of probiotics in cancer patients demonstrated that sepsis due to probiotics was rare [28]. The inclusion criteria of the PREP trial will filter out severely immunocompromised patients. Moreover, the strain of *Bacillus licheniformis* that will be used in the PREP trial has never shown toxicity in humans, but has reduced the incidence of diarrhea associated with antibiotic therapy [29]. One in vivo study suggested that this probiotic may carry a risk of antibiotic resistance [30].

The purpose of the PREP study is to provide high-level evidence on the use of probiotics for reducing the incidence of RIE. We anticipate that the rate of acute RIE will be significantly lower in the probiotic than in the placebo arm. We also expect that probiotics will decrease the incidence of chronic RIE and will have little or no toxicity in these patients.

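### The primary test uses neither sex, the only stratification factor, nor chemotherapy, the risk factor that sex stands in for: a valid test, but some precision is lost

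*Protocol article*

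**What the plan says.** Under Study aim and design, "participants will be randomly assigned 1:1 to the probiotics or placebo group using blocked randomization", after stratification by sex. The reason offered is: "Sex will be the single stratification factor, as patients with gynecologic malignancies have a greater tendency to require concurrent chemoradiotherapy". The same sentence adds that such treatment affects how often RIE occurs.

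In the Discussion, the largest earlier trial is criticised because it "did not provide information on chemotherapy, one of the major factors contributing to RIE".

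Under Data collection and follow-up period, "The primary endpoint will be the incidence of acute RIE". Under Sample size and statistical analysis, "Acute toxicities will be analyzed in the intention to treat population, with categorical variables in the two groups compared by the Chi-Square"; the alternative named is Fisher's exact test. No stratum or covariate is named for that comparison. A separate sentence follows: "To find the other confounding factors for RIE, univariate and multivariate logistic regression for acute toxicity will be performed". It lists no covariates.

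**The concern.** Sex was chosen only because it tracks chemoradiotherapy, and it tracks it loosely. The article claims no more than a greater tendency among gynecologic patients. The eligible sites also do not divide cleanly by sex: patients must "have histologically proven malignancies of the uterus, ovary, vagina, vulva, bladder, urethra, or prostate", so women with bladder or urethral cancer share a stratum with gynecologic patients. Beyond what sex explains, chemotherapy is balanced only by chance.

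The stated comparison then uses neither the proxy nor the factor behind it. Two things are at stake. One is the precision that comes from accounting for a strong predictor of the outcome. The other is the credibility of the result if the arms happen to differ in chemotherapy, because any adjustment would then be chosen after the imbalance had been seen. The article itself makes missing chemotherapy information a criticism of the largest earlier trial.

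**Working it through.** **The plan's own figure.** Inputs from Sample size and statistical analysis: 30% against 15%, alpha 0.05 (taken as two-sided), power 0.80. With unpooled variance, n = (1.960 + 0.842)² × (0.30×0.70 + 0.15×0.85) / 0.15² = 7.849 × 0.3375 / 0.0225 = 117.7, so 118 per group, as stated. Then 118 × 1.05 = 123.9, so 124 per group. The planned size reproduces, and the point below does not alter it.

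**Assumptions.** The article gives no sex mix, chemoradiotherapy share or chemotherapy effect. Base case: 70% women; chemoradiotherapy in 60% of women and 10% of men.

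**Chance imbalance in chemotherapy, 124 per arm.**
- Overall share: 0.7×0.6 + 0.3×0.1 = 0.45.
- Variance without stratification: 0.45×0.55 = 0.2475. SD of the arm difference = √(2×0.2475/124) = 6.3 points.
- Variance within sex: 0.7×0.6×0.4 + 0.3×0.1×0.9 = 0.195. SD = √(2×0.195/124) = 5.6 points.
- Stratifying by sex therefore removes 1 − 5.61/6.32 = 11% of the SD, or 1 − 0.195/0.2475 = 21% of the variance.
- Chance of a difference above 10 points: 10/5.61 = 1.78, two-sided normal tail about 7.5%.

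Varying women from 50% to 70% and chemoradiotherapy in women from 40% to 80%, with men at 10%, the SD reduction runs from 5% to 29%. The chance of exceeding 10 points runs from about 3% (50% women, 80%: SD = √(2×0.125/124) = 4.5) to about 8% (70% women, 50%: SD = √(2×0.202/124) = 5.7). A separate simulation with 118 per arm, up to 90% women and permuted blocks gave 6% to 13%.

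**Effect on the estimate.** With placebo risks of 40% with and 22% without chemotherapy (average 0.45×40 + 0.55×22 = 30.1%), a 10-point imbalance moves the risk difference by at most 0.10×18 = 1.8 points. A one-SD imbalance moves it by 0.056×18 = 1.0 point. The standard error is √((0.21 + 0.1275)/124) = 5.2 points.

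**Power.** 6,000 simulated trials of 248 patients per row, randomised within sex, probiotic halving the risk, base-case shares:

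| Placebo risk with/without chemotherapy | Odds ratio | Unadjusted | By sex | By sex and chemotherapy |
|---|---|---|---|---|
| 40% / 22% | 2.4 | 81.3% | 81.7% | 82.4% |
| 50% / 14% | 6.1 | 82.0% | 82.8% | 85.7% |
| 55% / 10% | 11 | 82.1% | 83.2% | 88.0% |

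Gains over the unadjusted test: 1.1, 3.7 and 5.9 points. Simulation error is about √(0.82×0.18/6000) = 0.5 points per figure. A repeat run of the same size gave gains of 0.3, 3.6 and 5.3 points, so the first row's gain is close to noise.

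In the separate simulation (118 per arm, chemotherapy odds ratio 3 to 5, randomisation by sex only), power rose from 79–80% unadjusted to 81–83% when the test was stratified by both factors.

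**Validity.** In that simulation, type I error of the unadjusted test was 4.6% to 5.5%, and the mean chemotherapy difference was at most 0.15 points.

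**The case against.** A reader might infer that chemotherapy is largely unbalanced by design, or that the result would be biased. The article does not support that. Allocation is 1:1, blocked within sex and generated centrally, so chemotherapy is balanced in expectation. The residual chance imbalance is already covered by the test's standard error.

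It is also fair to say that covariate-adjusted work is planned: a logistic regression for acute toxicity and a Cox model. An analysis plan that is not shown may list the covariates. But the logistic regression is worded as a search for confounders. Entry to the Cox analysis depends on a log-rank screen at p ≤ 0.2. Neither is the stated comparison of incidence, so they soften the point without removing it.

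The size argument largely stands. In the mildest scenario the gain is about 1 point, and the 6-point gain needs an odds ratio of 11, which nothing in the article supports. The claim that sex leaves most of the chemotherapy variation uncontrolled also depends on the assumed shares: with 50% women and chemoradiotherapy in 80% of women and 10% of men, sex leaves 0.125/0.2475 = 50.5% of the variance.

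Finally, the article does not say that the chemotherapy plan is settled at randomisation. Capsules start 2 weeks before radiotherapy, whereas CT simulation comes at most 10 days before it, so allocation precedes simulation. Recruitment was due to finish by 1 June 2021, so a change to the randomisation is probably too late.

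**Conclusion.** The point holds as a modest matter of efficiency and robustness. The article stratifies on a stand-in for a factor it calls major, then leaves both out of the stated primary comparison. Under the base-case shares, the residual imbalance has an SD of about 5.6 points, and a test stratified by sex and planned chemotherapy gains about 1 to 6 points of power over the unadjusted test. Stratifying by sex alone recovers about 1 point or less. All these sizes rest on assumed shares and risks. The planned test remains valid, and the sample size stands. Because the stated test can be improved at little cost, the change is worth making.

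**What to change.** Before unblinding, prespecify the primary acute comparison as a Mantel-Haenszel test, or a logistic model with treatment, sex and planned chemotherapy, stratified by:

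- sex; and
- planned concurrent chemotherapy (yes/no) as documented before randomisation. Chemotherapy actually received should not be used, because toxicity can alter it.

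First check, blind to allocation, that the plan was recorded before randomisation for every patient. If it was not, stratify by sex alone. If an unpublished analysis plan already specifies this, nothing more is needed.

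The cost is one sentence in the analysis plan and the check of baseline records. There will be four strata, and men with chemotherapy may form a small one: about 248 × 0.30 × 0.10 = 7 patients under the base case. No change to the randomisation is needed.

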**Fig. 1 Fig1:**
[figure not shown]
PREP study schema

### Inclusion criteria

Patients will be included if they [1] have histologically proven malignancies of the uterus, ovary, vagina, vulva, bladder, urethra, or prostate [2]; are aged > 20 years [3]; have an Eastern Cooperative Oncology Group performance score of 0–2 [4]; have an adequate hematologic condition within 6 months after enrollment, defined as absolute neutrophil count ≥1500 cells/mm^3^, platelet count ≥50,000 cells/mm^3^, and hemoglobin ≥8.0 g/dl [5]; have appropriate kidney function within 6 months after enrollment, defined as creatinine < 2.0 ng/dL; and [6] have appropriate liver function within 6 month after enrollment, defined as total bilirubin < 1.5 times the maximum normal value and alanine aminotransferase and aspartate aminotransferase < 2.5 times the maximum normal value.

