### Treatment implementation

Patients allocated to the probiotics group will be administered two Biscanen capsules (*Bacillus licheniformis* 250 mg containing 250 million colony forming units) three times per day, starting 2 weeks before the initial day of pelvic radiotherapy to the final day of radiotherapy. Patients in the placebo group will be administered placebo pills according to the same schedule.

Prior to radiotherapy, all patients will undergo enhanced computed tomography (CT) scans at 2.5 mm thickness. Participants should be relaxed and in a supine position facilitated by immobilization devices. Simulation CT images will be fused with the results of diagnostic magnetic resonance imaging or positron emission tomography-computed tomography in patients who require delineation of the prostate or gross target volume. Clinical target volume (CTV) will include pelvic regional nodal areas, based on the Asan Medical Center protocol for each tumor type. The upper margin for pelvic radiotherapy will be the junction of the 4th and 5th lumbar spine. The planning target volume (PTV) will include the CTV with 3–10 mm margins. Organs at risk, including the small bowel, large bowel, bladder, rectum, and femoral head, will be delineated according to the guidelines of the Radiation Therapy Oncology Group.

All patients will receive intensity modulated radiotherapy (IMRT) with the PTV required to be irradiated with ≥95% of the prescribed dose. Dose constraints will include the following: 1) 30% of the entire volume of the bowels (small and large) must not receive more than 40 Gy irradiation; 2) 60% of the volume of the rectum must receive ≤40 Gy; 3) 35% of the bladder volume must receive ≤45 Gy (except in patients with bladder cancer); and 4) 15% of the femoral head volume must receive < 35 Gy. Quality assurance will be performed before radiotherapy in all patients. During each treatment, cone-beam CT will be performed for image guidance. Radiotherapy will be scheduled to begin within 10 days after CT simulation, with the total radiotherapy period not exceeding 10 weeks.

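### As printed, the three laboratory inclusion criteria are dated after enrolment and the creatinine limit cannot be met, so they cannot do the entry screening that the Discussion relies on

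*Protocol article*

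**What the plan says.** The Inclusion criteria section of the protocol article lists six conditions. Three are laboratory conditions, and each carries a time window:

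- Blood counts (neutrophils, platelets, haemoglobin): "have an adequate hematologic condition within 6 months after enrollment".
- Creatinine: "have appropriate kidney function within 6 months after enrollment", with the limit printed as below 2.0 ng/dL.
- Bilirubin and transaminases: "have appropriate liver function within 6 month after enrollment".

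The Discussion mentions case reports of infection and sepsis from probiotics in immunocompromised cancer patients. Part of its answer is that "The inclusion criteria of the PREP trial will filter out severely immunocompromised patients".

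Under Treatment implementation the product is given "starting 2 weeks before the initial day of pelvic radiotherapy to the final day of radiotherapy", and radiotherapy is scheduled "with the total radiotherapy period not exceeding 10 weeks". Under Sample size and statistical analysis, "Acute toxicities will be analyzed in the intention to treat population".

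**The concern.** An inclusion criterion has to be decided on information available before the patient is randomised. A value obtained during the six months after enrolment cannot serve, because the patient is already in the trial and may already have taken the product. Values in that window can also be altered by radiotherapy and by the concurrent chemotherapy that the design section expects, particularly in gynaecologic patients.

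The creatinine limit has a separate fault. The unit exists, but the limit expressed in it is far below any value that a patient could have.

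What is at stake is mainly safety. The Discussion presents the inclusion criteria as the safeguard for giving live bacteria to cancer patients. If the blood-count criterion is not settled before the first dose, that safeguard is not in place as described. A lesser issue is that a criterion dated after enrolment invites the question of whether a randomised patient whose later values fail is still in the analysis.

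**Working it through.** **1. How often the window is wrong.** It appears in the haematology, kidney and liver criteria, which is 3 of 6. The same direction is printed each time, so it is not a single isolated slip. No other section gives a laboratory window that ends before enrolment.

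**2. What the window covers.** Inputs from Treatment implementation: product lead-in of 2 weeks; radiotherapy of at most 10 weeks.

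- Longest study treatment: 2 + 10 = 12 weeks.
- Six months is about 26 weeks.
- If treatment starts at enrolment (an assumption; the article does not fix the interval), the window covers all of treatment and about 26 − 12 = 14 weeks more.

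A qualifying value could therefore be taken before, during or after treatment.

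**3. The creatinine limit.** 1 mg = 1,000,000 ng, so 2.0 ng/dL = 2.0 / 1,000,000 = 0.000002 mg/dL. That is one million times below the same number in mg/dL. Nowhere else does the article give a creatinine limit or unit.

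**4. The two sections side by side.** The Discussion says that the inclusion criteria screen out the severely immunocompromised. Among the laboratory limits, the neutrophil count is the one that bears directly on this; creatinine, bilirubin and transaminases do not. Dated after enrolment, the neutrophil limit cannot act before the first dose. The two printed faults also pull in opposite directions: the window screens nobody out at entry, while the creatinine limit lets nobody in.

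**5. Is the sample size touched?** First the plan's own figure. Inputs: "30% of the patients in the placebo group and 15% of the patients in the probiotics group", alpha 0.05 (taken as two-sided), beta 0.2. With the unpooled-variance formula:

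n = (1.960 + 0.842)² × (0.30 × 0.70 + 0.15 × 0.85) / (0.30 − 0.15)² = 7.849 × 0.3375 / 0.0225 = 117.7, rounded up to 118 per group.

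This matches the stated 118. For dropout, 118 × 1.05 = 123.9, which gives the stated 124 (118 / 0.95 = 124.2 is practically the same). None of these inputs depends on the laboratory window or the creatinine unit, so correcting them leaves 118 and 124 per group unchanged.

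**The case against.** The strongest reply is that these are slips of wording with no demonstrated effect. The section is by its nature an entry rule, and the design section has patients screened before consent and randomisation, so a misprinted preposition is a natural reading. Recruitment began on 1 June 2019, so the creatinine limit is evidently not applied as printed. Histology, age, performance status and the exclusion criteria can all be applied at entry. This largely stands: both faults are probably drafting errors, and screening as a whole has not failed. It does not remove the point, because these are operative thresholds, nothing in the article corrects them, and the Discussion rests a safety argument on them.

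A reader might infer something stronger: that the wording builds in outcome-related exclusion after randomisation, with bias and loss of power. The documents do not support that. No section says that a later laboratory value removes a patient. The Dropout criteria do not name a failed laboratory criterion; their rule on medical issues and grade 3 or higher toxicity is a separate matter. Acute toxicities are already analysed by intention to treat. The article gives no rate of later laboratory failure, so any power figure is illustration only: removing 5%, 10% or 20% of 124 per group would lower power from 81.1% to 79.1%, 76.9% or 71.9% (pooled-variance formula). Nothing in the plan says that any such removal would happen.

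**Conclusion.** The point holds as an error in the printed eligibility criteria. Three of six inclusion criteria carry a window that cannot decide entry, and one of them also carries a limit of 0.000002 mg/dL that no patient could meet. Together they contradict the Discussion's reliance on the inclusion criteria before a live-bacteria product is given, with the direct safety link confined to the neutrophil limit.

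It should be corrected, but it does not undermine the design. Exclusion after randomisation is left open by the wording, not prescribed; the intention-to-treat statement limits any effect on the primary analysis; and the sample size is unaffected. The conclusion assumes that the article reproduces the operative criteria. If full protocol version 1.6 has the window and unit right, the fault lies in the article alone.

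**What to change.** Reconcile the Inclusion criteria section with full protocol version 1.6:

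1. Make all three laboratory windows end before randomisation. The sponsor should set their length. Merely reversing the direction may not be enough, since a count up to six months old may not describe the patient at the first dose.
2. Correct the creatinine unit against the full protocol.
3. Confirm that laboratory values after randomisation remove no one from the intention-to-treat population already specified.
4. Record which laboratory values and dates were actually used at entry.

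No clinical threshold is proposed here. The cost is a wording correction in the article and, if the full protocol has the same text, an amendment. Recruitment was expected to finish by 1 June 2021, although the article, published on 16 September 2021, still calls it ongoing. The first two items may therefore come late for screening; the last two remain useful at any time before analysis.
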